#### Registration and enrolment visit

The registration visit will be used to screen, assess eligibility and enrol participants that meet the eligibility criteria. Demographic data, ocular and medical health history and biometry using the LenStar LS 900 will be taken. Biometry data will be used to determine the basis of anisometropia. Optical Coherence Topography Scans of the macular (3D macula: 7 × 7 mm) and retinal nerve fibre layer (3D Optic Disc 6 × 6 mm scan) will be taken using the DRI Triton Optical Coherence Topographer to confirm eye health. Cover testing is performed at near and distance to screen for strabismus, but visual acuity, fusional vergence/peripheral fusion, ocular motility and stereopsis will only be assessed if this information is not available from the referrer. Eligible participants will then be randomly allocated to either the control or the treatment group.

#### Randomisation

Participants will be randomised to the control standard lenses group or treatment aniseikonia-correcting lenses group after they are confirmed to be eligible for the trial and have consented to take part. Allocation to each group will at a 1:1 ratio using a computer-generated randomisation schedule [39] by an unmasked study member. The schedule was generated using randomised permuted blocks with fixed block sizes. The block sizes will not be disclosed to ensure concealment. Unmasked study staff will perform spectacle dispensing to ensure correct fitting and make all spectacle adjustments required at data collection visits.

### Appointment schedule

#### Baseline visit

The baseline visit is when participants collect their new spectacles. This visit contains the first aided visual acuity and binocular function assessment. A minimum of 15 min of adaptation time to the new spectacles will be given before vision testing is commenced. To allow adaptation time, testing is to be carried out in the following order:
Dispensing and spectacles fitting by unmasked examinerParent and child to complete PedEyeQ questionnaireSpectacle adherence diary given and explainedDistance visual acuity test using the EVA testerCover test with refractive correction in place at 33 cm and 6 mCover test without refractive correction at 33 cm and 6 mOcular motilityHorizontal fusional vergence range test using prism fusion range at 33 cm and 6 m.If horizontal fusional vergence range testing is not possible, then peripheral fusion will be assessed using the 20Δ base out test in front of either eye. If a 20Δ prism is not overcome, then a 10Δ base out prism will be used.Vertical fusional vergence range test using the prism fusion range at 6 mStereopsis using the Randot Preschool stereotestAniseikonia Inspector V3The New Aniseikonia Test (Awaya)

The PedEyeQ questionnaire will be used to assess functional vision and eye-related quality of life (ER-QOL) in children and their parents [40]. Following the baseline visit, participants will be asked to wear their spectacles full-time until they have completed 15 weeks of spectacle wear.

#### 5-week, 10-week and 15-week follow-up visits

Participants will be required to attend three 20-min follow-up visits, at 5, 10, and 15 weeks from baseline. At each follow-up visit, a research orthoptist masked to the child’s treatment allocation will assess visual acuity, stereopsis, ocular alignment, near point of convergence, horizontal fusional vergence range or 20Δ base out test for peripheral fusion, bifoveal fixation using the 4 Δ base out reflex test and visuoscopy. Subjective aniseikonia will be reassessed at the 15-week follow-up visit only. Adherence with spectacle wear will be monitored by completing a daily spectacle wear diary which will be checked and encouraged at each follow-up visit. Objective monitoring with the SpecsOn spectacle-mounted adherence monitor will be removed after a minimum of 5 weeks. However, if participants are willing, this may be extended to 10 weeks.

#### Intervention

Participants are allocated to one of two groups, either the control group (standard spectacles) with lenses that correct only refractive error, or the treatment group (iseikonic spectacles) where lenses incorporate aniseikonia correction as well as refractive correction. Participants will be provided with spectacles at no cost to them for fulltime wear for 15 weeks and will be able to keep these spectacles after study participation. Aniseikonia correction will be provided using SHAW lenses (Canada) (https://shawlens.com) through the local Australasia distributor, CR Surfacing labs. Standard amblyopia Shaw lens ordering procedures will be followed. Iseikonic lenses are sometimes used in optometry practices in New Zealand and overseas for optical correction in children and adults with anisometropia to help reduce visual discomfort and aid in adaptation. The optional objective spectacle monitoring device [38] will be fitted to the spectacle frames and parents of all participants will be asked to complete a daily spectacle wear diary to monitor adherence.

#### Intervention modifications and adherence

Asthenopia can result from adaptation to new lenses and may initially cause some discomfort, but this should improve within the first few weeks and persistence with the spectacles will be encouraged. Adherence to spectacles will objectively be monitored for the first 5 weeks, but participants will fill out a daily spectacle wear diary for the full 15 weeks where they will be required to record times when spectacles were removed, the duration without spectacles and the activities that required them to remove the spectacles. Diary entries will be checked and encouraged at all follow-up visits. No other concomitant therapy for amblyopia or alternative refractive correction is allowed for the full 15-week period.

#### Masking

The clinical examiner, participants and their parents will remain masked to treatment allocation throughout the whole study. Personnel involved in recruitment, data collection (assessing the outcomes) and those involved with data entry, data cleaning and analysing the results will also be masked until the code is broken after data lock. Masked clinical examiners may be able to identify treatment allocation if they look closely at the spectacles. Therefore, masked clinical examiners will not handle the spectacles at all. Any adjustments required to the frames or assessment of repairs will be performed by unmasked study staff, who do not conduct any clinical examinations. Participants and parents/caregivers attending visits will also be instructed that the masked clinical examiner will not be able to answer any questions about their lenses. Participants will be informed about their group allocation by letter/report once all data has been collected and analysed.

#### Study schedule

The study schedule has been summarised in Fig. 1.

**Fig. 1 Fig1:**
[figure not shown]
Schematic summary of the MAGNIFY schedule of enrolment, interventions, and assessments

### Data collection

#### Outcome

Outcome measures will be assessed at 5-, 10-, and 15-week post-randomisation by a masked clinical examiner. All study members will be trained on study requirements. Masked clinical examiners will use standard clinical measurements to complete paper-based data collection forms designed by study investigators. Baseline and outcome measures are summarised in Table 1. A trial management team will be checking the integrity of data collected on the paper forms as they are entered onto the database to ensure data quality and completeness.

**Table 1 Tab1:** Schedule of tests and follow-up visits

Measures	Registration	Baseline assessment	5 weeks	10 weeks	15 weeks
Demographics	✓				
Visual acuity	✓^a^	✓	✓	✓	✓
Ocular alignment	✓	✓	✓	✓	✓
Motor fusion	✓^b^	✓	✓	✓	✓
Stereopsis	✓^b^	✓	✓	✓	✓
Subjective aniseikonia tests		✓			✓
Biometry	✓				
OCT	✓				
PedEyeQ		✓			✓
Serious adverse events			✓	✓	✓
Spectacle adherence			✓	✓	✓
Allocation	✓				

^a^Unaided visual acuity is measured at the registration visit if not available from the referrer. The Keeler LogMAR chart will be used in the study for those who require measurement at the registration visit

^b^Tests done by study clinicians only if relevant information is not available from the referrer

#### Primary outcome

The primary outcome measure will be change in amblyopic eye VA from baseline to the 15-week outcome visit, measured using the highly standardised HOTV protocol on the electronic visual acuity (EVA) testing system [23].

#### Secondary outcomes

Change from baseline in distance visual acuity of the amblyopic eye at 5- and 10-week post baseline assessmentChange from baseline in distance visual acuity of the fellow eye at 5, 10 and 15 weeksChange from baseline in interocular acuity difference at 5, 10 and 15 weeksChange from baseline in stereopsis at 5-, 10- and 15-week follow-up visits, measured using the highly standardised Randot Preschool stereotest [25]Spectacle wear adherence at 5-, 10- and 15-week visits, measured using the daily spectacle-wear diaryPedEyeQ quality of life metric questionnaire to assess functional vision and eye-related quality of life (ER-QOL) in children and their parents [40]

### Participant retention

Once a child is randomised, study staff will make every possible effort to follow the child for the entire study period. Reminders of upcoming study visits will be sent via the preferred method of communication indicated at the enrolment visit and contributions will be made towards travel costs for each visit.

### Conclusion of the study

At the end of the 15-week study period, all participants will be referred back to the eye care provider that referred them with a full report of their status. If vision in the amblyopic eye has not sufficiently improved after 15 weeks of fulltime spectacle wear, further amblyopia treatment (such as patching therapy) will be provided by referral to the appropriate eye care provider. Any adverse events to the participant and/or spectacles will be monitored and recorded as appropriate.

### Sample size

A sample size of 50 patients (25 per arm) will provide 95% power at *p* = 0.05 to detect a minimal clinically important difference of 0.20 log units improvement in visual acuity as tested on the EVA test [41, 42] at 15 weeks, assuming a standard deviation of 0.17 [43]. This sample size allows for an overall loss-to-follow-up of 15% [44] (calculated using GraphPad Sat Mate 2.0).

### Data management

All participants will be assigned a unique identification code to protect confidentiality immediately following data collection. All clinical data will be collected, recorded, stored and analysed under this unique research code. All paper-based clinical documents will be safely stored in a locked secure cabinet at the School of Optometry and Vision Science for 6 years before being securely destroyed. De-identified electronic data will be stored indefinitely on password-protected computers to allow comparison to future data sets. Consent forms and referral letters, which contain identifying information, will be held in a secure location, separate from the research data for a period of 6 years.

### Data analysis

Statistical analyses will be performed using SAS version 9.4. All statistical tests will be two-tailed and at a 5% significance level throughout the analyses, and all treatment evaluations will be performed on the principle of ‘intention to treat’ unless otherwise specified. The ITT population will consist of all randomised participants according to their randomised group, regardless of the treatment actually received and subsequent withdrawal or deviation from the protocol. People who subsequently withdrawal from the study will contribute their data already collected in the ITT analysis. A per protocol analysis will also be performed on the primary outcome to assess the robustness of the results. Randomised participants who have no major protocol violations will be included in this subset for analysis. Relevant protocol violations may include errors in treatment assignment, the use of excluded medication, poor compliance, loss to follow-up and missing data. For this trial, possible conditions of major protocol violation include:
Poor spectacle wear compliance (< 75% of waking hours)Loss to follow-up and missing outcomeFollow-up visits fall out of time window: out of ± 7 days for 5-, 10- and 15-week follow-up visits

The study investigators will conduct a blinded review of all participants with protocol violations before final data analysis and make decision on the list to be excluded from the per protocol set. Participants that withdraw will contribute data to the point of withdrawal unless data withdrawal is specifically requested. No adjustments for multiple comparisons are planned for any of the outcomes. No imputation will be performed for missing data.

All results will be presented overall and by treatment groups. Summaries of continuous variables which are normally distributed will be presented as means and standard deviations or medians and inter-quartiles for skewed data, while categorical variables will be presented as frequencies and percentages.

For logMAR visual acuity, smaller or more negative values equal better vision. For this study, change from baseline (0 week) to follow-up in distance visual acuity of the amblyopic eye will be calculated as (baseline–follow-up). Positive change from baseline values indicates there is improvement, and negative values indicate worsening of the condition.

When the method of mixed model for repeated measure (MMRM) is used, the model will include treatment, time, treatment by time interaction, baseline value as fixed effects and subject as random effect, unless otherwise stated. The within-subject errors will be modelled using an appropriate covariance matrix. Candidate structures include but are not restricted to unstructured, autoregressive, Toeplitz, compound symmetry and spatial. Kenward-Roger method will be used to estimate the denominator degrees of freedom for fixed effects.

The results will be published in journals and through conference presentations to the relevant professional groups. Participants can choose to receive a summary of the overall trial results by letter/report once all data has been collected and analysed. This is an option on the consent form.

### Data monitoring

An independent monitor will check the existence and correct date for all signed consent forms. The monitor will also sample over 10% of all randomised participants to check accuracy of data on the database against source data. This trial is considered to be low risk and, therefore, establishing a Data Safety Monitoring Committee for the trial is not necessary.

Interim analysis is performed when 50% of the patients have been randomised and completed the 15 weeks follow-up. The interim analysis is performed by an independent statistician, masked to treatment allocation.

### Harm

We do not expect any adverse effects to arise from the lenses in this study, as both types of lenses are currently used in New Zealand and overseas in the treatment of anisometropic amblyopia in children. Normal spectacle lenses have been shown to resolve amblyopia in 30% of children and no adverse effects have been reported [6, 7, 45]. Aniseikonia lenses have been found to reduce asthenopic symptoms (headaches/eyestrain/blurry vision) that are normally associated with adapting to a new prescription in adults [46], and there have not been any reports of adverse effects from clinical use in children.

Adverse events unrelated to the study treatment may occur, e.g. circumstances that prevent the child wearing their glasses such as illness or broken glasses. These events will be documented and monitored closely throughout the clinical trial.

All adverse events and spectacle related incidents occurring during the trial and that are observed by study personnel or reported by the participant will be recorded, whether or not attributed to trial treatment. Adverse events will be collected systematically at each follow-up visit and open-ended questioning will encourage participants to report on unexpected adverse events. Those that are considered related to the trial treatment as judged by a qualified investigator will be followed either until resolution or the event is considered stable. It will be left to the judgement of the qualified study investigators to decide whether or not an adverse event is of sufficient severity to require discontinuing the participant from the study. A participant may also voluntarily withdraw from participating in the study due to what he or she perceives as an intolerable adverse effect. If either of these occurs, the participant will undergo follow-up visits for trial assessment and be given appropriate care under medical supervision until symptoms cease, or the condition becomes stable.

An independent monitor will review the source documents (paper data collection forms) and determine whether the data reported in the database system are complete and accurate. Quality assurance of the lenses and spectacles will be undertaken by the unmasked team members that are responsible for ordering lenses and quality checking them for correction prescription and lens allocation.

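### The Harm section promises trial visits after an adverse-effect withdrawal, but the Data analysis section, read literally, counts data only up to the withdrawal

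*Protocol article*

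**What the plan says.** The Harm section of the protocol article describes two routes out of the study. In the first, investigators "decide whether or not an adverse event is of sufficient severity to require discontinuing the participant from the study". In the second, the family decides: "A participant may also voluntarily withdraw from participating in the study due to what he or she perceives as an intolerable adverse effect". For both routes the section then says: "If either of these occurs, the participant will undergo follow-up visits for trial assessment". That sentence also provides for medical care, and the only end point it names is that the symptoms have resolved or the condition has settled.

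The Data analysis section states the rule for withdrawals twice: "People who subsequently withdrawal from the study will contribute their data already collected in the ITT analysis", and later "Participants that withdraw will contribute data to the point of withdrawal unless data withdrawal is specifically requested". It adds that missing data are not imputed. The same section defines the ITT population as every randomised child in the allocated group, whatever treatment was received and whatever withdrawal followed.

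Two other sections bear on follow-up. Participant retention says that after randomisation "study staff will make every possible effort to follow the child for the entire study period". The section on follow-up visits says: "Participants will be required to attend three 20-min follow-up visits, at 5, 10, and 15 weeks from baseline". The primary outcome is the change in amblyopic-eye acuity from baseline to the 15-week visit.

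**The concern.** Site staff and the analyst receive different instructions about the same child. Staff are told to continue trial assessments after an adverse-effect exit. The analyst, taking the withdrawal sentence at face value, stops that child's data at the exit. The ITT definition and the retention promise point towards keeping the child in. No section says which instruction governs these assessments. It is also not clear that the Harm visits reach week 15, because the only end point in that sentence is resolution or stability of symptoms.

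This matters more here than in most trials because the interventions are expected to differ in comfort. The abstract's discussion and the secondary objectives suggest that aniseikonia correction may reduce discomfort and improve adherence. The Harm section cites fewer asthenopic symptoms with such lenses in adults. The Spectacle adherence section links wear time to visual gain. Leaving the study because the lenses are not tolerated could therefore be related both to arm and to the 15-week acuity. Leaving out those outcomes, when the protocol plans to collect them, would put an avoidable bias into the primary comparison.

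**Working it through.** **1. The passages side by side, for a child who leaves the study because of an adverse effect**

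| Question | Harm | Data analysis | Participant retention |
|---|---|---|---|
| Are trial assessments made after the exit? | Yes | Not addressed | Every effort, for the whole study |
| Until when? | Symptoms cease or are stable, if that phrase governs the visits and not only the care | Not addressed | End of study |
| Do later acuities count in ITT? | Not addressed | On a literal reading of the withdrawal sentence, no; on the ITT definition, yes | Not addressed |

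The withdrawal rule covers every withdrawal, whatever the reason. It collides with the Harm section in particular because that section expressly promises further assessments after an exit. The rule is worded for participants who withdraw, and whether it also covers a child discontinued by the investigator is open.

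**2. The plan's own sample size, as a reference**

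Inputs from the Sample size and Data analysis sections: difference 0.20, SD 0.17, two-sided 5%, power 95%, loss 15%, total 50.

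- Normal approximation: n per arm = 2 × (1.960 + 1.645)² × 0.17² / 0.20² = 18.8, so 19.
- Two-sample t-test: 20 per arm, power 95.2%. Total = 40 / 0.85 = 47.1, so 48 in equal arms. The stated 50 is consistent with this.
- After 15% loss: 50 × 0.85 = 42.5, about 21 per arm, power 96.1%.

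**3. Possible shift in an arm mean (assumption)**

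The protocol gives no rate of withdrawal for intolerance and expects no adverse effects from the lenses. Assume that k of 25 children in one arm are left out, and that their true mean 15-week gain is d below that of the children retained. An observed-case mean then overstates the arm's gain by (k/25) × d.

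- Low end: 1/25 × 0.10 = 0.004 logMAR, which is 0.004/0.20 = 2% of the target difference.
- High end: 4/25 × 0.20 = 0.032 logMAR, which is 0.032/0.20 = 16%.

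**4. Direction**

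Take a true difference of 0.20 and the high end. If the children left out are controls, the control gain is overstated and the expected difference falls to 0.20 − 0.032 = 0.168. If they are in the treatment arm, it rises to 0.20 + 0.032 = 0.232. The protocol's own expectation of better comfort with aniseikonia correction points to the first case, towards the null.

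**5. Power**

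If such losses come on top of the 15%, power is 95.6% with 1 lost (20 against 21) and 93.9% with 4 lost (17 against 21). Power is not the issue. The issue is possible bias and which children the estimate describes.

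**6. What a mixed model would recover**

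Where the repeated-measures model is used, baseline enters as a covariate. A child with a week-5 or week-10 value before leaving still contributes, on the assumption that the data are missing at random, which exits for intolerance could breach. A child with no post-baseline value adds nothing to the treatment comparison. The section on intervention modifications says that adaptation discomfort should improve within the first few weeks. It does not say that children leave before week 5, so how often this would happen is unknown.

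**The case against.** The strongest reply is that the withdrawal sentences are retention rules. They contrast with families who ask for their data to be removed, and they say that what has been collected is kept. Neither sentence says that only such data count or that later data are excluded. This stands. A reader might infer that the plan bars post-withdrawal assessments from ITT, but the text does not go that far. The exclusion is a literal reading, and the opposite reading is also available. That two readings are possible is the defect.

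Second, stopping the spectacles is not the same as leaving the study. Wear below 75% of waking hours is listed as poor compliance and a possible per-protocol violation, and ITT keeps the child regardless of treatment received. This also stands. The point is limited to children who are discontinued from, or withdraw from, the study itself.

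Third, the phrase on symptom resolution may attach only to the medical care, with the trial visits running to week 15 as scheduled. That is a fair reading, but the sentence does not settle it.

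Fourth, a reader might infer that the plan conceals a difference in tolerability. It does not. Adverse events and spectacle incidents are all recorded, adherence and PedEyeQ are secondary outcomes, and results are presented by treatment group.

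Finally, the handling of data after discontinuation may be set out in an analysis plan or in the withdrawal appendix, neither of which is shown. Silence on such detail would be no finding. Here, however, the article itself states rules that do not fit together.

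**Conclusion.** The conflict is real and should be resolved. For children who leave the study because of an adverse effect, the Harm section plans further trial assessments, while the Data analysis section, read literally, ends their data at withdrawal, against the ITT definition and the retention promise. Primary-outcome data that the protocol plans to collect may be left out of the ITT analysis, and the loss may be related to arm and outcome.

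It would be too strong to say that 15-week outcomes are lost selectively. The documents give no rate, expect no adverse effects and do not fix the timing of exits. The range of 0.004 to 0.032 logMAR (2% to 16% of the target difference) rests wholly on the assumed 1 to 4 children of 25, the assumed deficit of 0.10 to 0.20 logMAR and an observed-case analysis. If the protocol's expectation about comfort is right, the bias runs towards the null and works against the trial's own hypothesis.

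**What to change.** Reconcile the Harm and Data analysis sections with three statements:

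- A child who stops the study spectacles, or is discontinued from the study, for an adverse event is asked to attend the remaining scheduled visits through week 15, whenever symptoms resolve, unless the family declines.
- Acuities from these visits enter the ITT analysis under the allocated arm.
- The rule that data count up to the point of withdrawal applies only where the family withdraws consent to follow-up.

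This concerns only which visits are sought and which data are counted. The care of such a child, including any decision about the spectacles, stays with the investigators.

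The cost is a wording amendment. The visits are already scheduled, and the Harm section already promises follow-up. The one drawback is that some acuities measured after a child has stopped the lenses enter the comparison and may dilute it slightly, which the ITT definition already accepts.
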